##### *Safety assessments*

##### Safety assessments will consist of monitoring and recording of all non-serious and serious adverse events and regular monitoring of blood chemistry, regular measurement of vital signs, and performing of physical examination and body weight estimation. Patients will be monitored for signs of adrenal insufficiency and will be educated on how to manage adrenal insufficiency and will carry a steroid card and will have a supply of 1mg oral dexamethasone to use in the event of symptoms (see above 2.3). A safety sheet assessment will be filled in at each visit by the investigator whilst on treatment.

Safety population – all patients who received at least one dose of Mifepristone will be considered for the safety evaluation.

### *Safety Evaluation* *- Adverse Drug Reactions*

Safety analysis will be performed on the safety population as defined above. The assessment of safety will be based mainly on the frequency of adverse events and on the number of laboratory values that fall outside the predetermined ranges. All adverse events will be listed. Adverse events will be summarised and presented with the number and percentages of patients having any adverse event and having an adverse event in each body system. Any other information collected (e.g. severity or relatedness to the study medication) will be listed as appropriate, and assessed by the investigator, co-investigator and steering committee. It is not anticipated that the use of mifepristone will be associated with severe adverse events. However, any such event will be reported to the STH Research Department within 24 hours, and any Suspected Unexpected Serious Adverse Reaction will be cascaded to the MHRA and Research Ethics Committee.

An adverse event (AE) can be any unfavourable and unintended sign (including an abnormal laboratory finding), symptom, or disease temporally associated with the use of a medicinal product, whether or not considered related to the medicinal product. All noxious and unintended responses to an IMP (i.e. where a causal relationship between an IMP and an adverse event is at least a reasonable possibility), related to any dose should be considered adverse drug reactions. For marketed medicinal products, a response to a drug which is noxious and unintended and which occurs at doses normally used in man for prophylaxis, diagnosis, or therapy of diseases or for modification of physiological function, is to be considered an adverse drug reaction. An unexpected adverse drug reaction is defined as an adverse reaction, the nature or severity of which is not consistent with the applicable product information (e.g. Investigator’s Brochure for an unapproved IMP).

### Serious Adverse Events (SAEs)

A serious adverse event (SAE) is defined as any untoward medical occurrence that at any dose either:-

• results in death

• is life threatening

• requires inpatient hospitalisation or prolongation of existing hospitalisation

• results in persistent or significant disability/incapacity (disability is defined as a

substantial disruption of a persons ability to conduct normal life functions)

• is a congenital anomaly/birth defect.

Important medical events that may not result in death, be life-threatening, or require hospitalisation may be considered a serious adverse drug experience when, based upon appropriate medical judgement, they may jeopardize the patient or patient and may require medical or surgical intervention to prevent one of the outcomes listed in this definition. Examples of such medical events include allergic bronchospasm requiring intensive treatment in an emergency room or at home, blood dyscrasias or convulsions that do not result in inpatient hospitalisation, or the development of drug dependency or drug abuse. Instances of death or congenital abnormality, if brought to the attention of the Investigator at any time after cessation of the study treatment and considered by the Investigator to be possibly related to the study treatment, will be reported to the sponsor.

Definition of Life Threatening:

An adverse event is life threatening if the patient was at immediate risk of death from the event as it occurred, ie. does not include a reaction that might have caused death if it had occurred in a more serious form. For instance, drug induced hepatitis that resolved without evidence of hepatic failure would not be considered life threatening even though drug induced hepatitis can be fatal.

Definition of Hospitalisation

Adverse events requiring hospitalisation should be considered serious. In general, hospitalisation signifies that the patient has been detained (usually involving an overnight stay) at the hospital or emergency ward for observation and/or treatment which would not have been appropriate at the CRF. When in doubt as to whether hospitalisation occurred or was necessary, the adverse event should be considered as serious. Hospitalisation for elective surgery or routine clinical procedures, which are not the result of an adverse event, need not be considered adverse events and should be recorded on a Clinical Assessment form and added to the Case Report Form. If anything untoward is reported during the procedure, this must be reported as an adverse event and either ‘serious’ or ‘non-serious’ attributed according to the usual criteria.

### SAE Reporting

STH R & D, the sponsor, will be responsible for coordinating the reporting of SAEs.

The Investigator will be responsible for completing an SAE report form and forward by fax to the sponsor immediately (within 24 hours) of becoming aware of an SAE.

The responsibilities of the sponsor include the following:-

• Prepare an adverse event reporting plan prior to the start of the study.

• Receive and review SAE report forms from the Investigator.

• Write case narratives and enter the case into the sponsor’s safety database

• Produce appropriate reports of all Suspected Unexpected Serious Adverse Reactions (SUSARs) and forward to the IEC, MHRA and the Principal Investigator.

Laboratory data will be summarised by presenting summary statistics of raw data and change from baseline values (means, medians, standard deviations, ranges) and the flagging of notable values in data listings.

Data from other tests will be listed. Notable values will be flagged. Any other information collected will be listed as appropriate.

#### *Efficacy*

Intention to treat population (ITT) - All patients who received at least one dose of Mifepristone and from whom at least one efficacy measurement is obtained after the study treatment start.

Protocol population (PP) - All patients who complete the study without any major violations of the protocol procedures.

##### *Efficacy evaluation*

The primary efficacy analysis can be run on both the ITT and PP populations in order to take into account the response of patients prematurely withdrawing from the study for any reason.

The primary efficacy evaluation is based on the primary efficacy parameters given. In cases of premature withdrawal from the study, at least one post-baseline measured efficacy parameter will be carried forward. The primary efficacy variable is then derived as the proportion of patients with successful treatment outcome after 8 weeks using the following criteria to define treatment outcome:

i) change in the resting and 24-hour ambulatory blood pressure.

ii) change in 2-hour glucose on OGTT.

*Safety of investigators* – There are no specific issues

*Participants rights to information and consent, confidentiality and privacy*

This will be in accordance to GCP guidelines. In terms of informed consent, patient recruitment will be at time after completion of usual investigation according to clinical practice. Since there is no specific time window needed for intervention, potential participants will have adequate time to consider their involvement and what it entails.

*Storage of data*

Patient data will be in a secure repository for 15 years.

*Ethnic and racial diversity*

This is a pilot study and thus the numbers are small. There is no evidence of altered adrenal function in different ethnic groups. In terms of information and consent if any potential study participant is not fully competent in the English language appropriate interpreters and translation of the information sheet and consent will be undertaken. Given the predominant Caucasian population of our catchment area it is likely that the participants will be Caucasian.

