***Drug administration and compliance****:* A check on the blister packs of the tablets issued and therapeutic drug monitoring will be performed at each visit to assess and encourage compliance. All existing medication will be left unaltered for the duration of the study. The first dose of the drug (Treatment start) will be given at Visit 2 (week 0) after baseline tests have been performed. The last dose (Treatment end) will be taken in the morning at Visit 8 (week 8). The drug will be administered 1 hour before food to maximise bioavailability as mifepristone is absorbed rapidly.

***Safety****:* Clinical assessment by BP, P, temperature, weight and questioning for fatigue, headache, anorexia, nausea, arthralgia, myalgia, and abdominal pain (potential glucocorticoid deficiency, a predictable effect of mifepristone based on its known action) will be made at each study visit. Clinical experience is, however, that even total adrenal insufficiency is well tolerated in the absence of physical or infective stressors. For safety purposes each patient will also be issued with written instructions which will tell them what to do if this side effect occurs and with a supply of two dexamethasone 1mg tablets (sufficient to overcome the effects of mifepristone 400mg by taking dexamethasone 1mg/day for 2 days) to be taken on the advice of the investigators if significant symptoms are reported. In such circumstances any study subject will be asked to attend the CRF either that day or the next working day, and data entered into the CRF accordingly, and the subject asked to stop the mifepristone and withdrawn. Other uncommon but documented side effects of mifepristone used at this dose and for this time period include: skin rash (maculopapular), increased eosinophil count, joint pain, hypokalaemia. When used for >3-6 months duration endometrial hyperplasia, uterine fibroma, and endometriosis are described.

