**5.4 Outcome measures**

***Primary end points*** will be the difference at 8 weeks, compared to baseline, in systolic blood pressure (BP) (resting and ambulatory) and 2-hour glucose tolerance during a 75g oral glucose tolerance test. BP will be measured in the sitting position, left arm taken twice, separated by 5 mins, after 10 mins resting (according to British Hypertension Society, UK [BHS] guidelines). 24-hour ambulatory blood pressure will be measured using standard BHS-approved monitors.

The primary endpoints have been chosen, as they are associated with important clinical outcomes. Baseline 24 hour ambulatory BP monitoring will be performed in the week starting treatment between the first visit (screening) and second visit (treatment start) and again at weeks 4 and 8. The daytime and nocturnal BP as determined by 24-hour ambulatory monitoring will be assessed independently and together to take account of the influence of the circadian rhythm in serum cortisol. The baseline glucose tolerance test will be performed on the first day of treatment (treatment start) before the first dose and again at weeks 4 and 8.

***Secondary end points*** will be compared to baseline: 1) the difference in BP and Glucose tolerance at 4 weeks; 2) homeostasis model assessment of insulin resistance (HOMA-IR) 42, and the insulin Sensitivity Index (ISI) 43 at 4 and 8 weeks, as calculated from oral glucose tolerance test: insulin and glucose at -15, 0, 30, 60 and 120 minutes, with oral glucose 75g at time 0 (except for those on insulin therapy, whose investigation will be limited to basal and 120 minute plasma glucose); 3) the difference in the mean plasma 0900h plasma ACTH, and salivary 0900 and 2400h cortisol values at 4 and 8 weeks; 4) the difference in fasting lipids at 8 weeks; 5) the difference in bone turnover markers at 8 weeks; 6) difference in urinary steroid profile at week 8; 7) the difference between depression, quality of life and fatigue questionnaires at 4 and 8 weeks. Tertiary endpoint will be any major cardiovascular adverse events at 8 weeks. Other biochemical safety parameters are summarized in the table above.

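### The carry-forward rule lets a reading from week 4, or for resting BP as early as week 1, stand as the 8-week outcome of a withdrawn patient, and does not exclude readings taken after dexamethasone

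*Protocol*

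**What the plan says.** Section 5.4 sets the time point. The primary end points "will be the difference at 8 weeks, compared to baseline, in systolic blood pressure (BP) (resting and ambulatory", and in 2-hour glucose on a 75 g OGTT. Baseline ambulatory BP is taken "between the first visit (screening) and second visit (treatment start) and again at weeks 4 and 8". The OGTT is done "before the first dose and again at weeks 4 and 8". The week-4 differences in BP and glucose tolerance are listed separately as the first secondary end point.

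Section 8.0 (Efficacy evaluation) gives the rule for early leavers: "In cases of premature withdrawal from the study, at least one post-baseline measured efficacy parameter will be carried forward". It continues: "The primary efficacy variable is then derived as the proportion of patients with successful treatment outcome after 8 weeks". Entry to the ITT set needs one dose and a patient "from whom at least one efficacy measurement is obtained after the study treatment start". On populations, "The primary efficacy analysis can be run on both the ITT and PP populations", with the stated aim of allowing for early withdrawals.

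Section 5.2 (Safety) has BP taken at every visit, and section 5.8 makes visits weekly to week 4, then at weeks 6 and 8. Section 5.2 calls possible glucocorticoid deficiency a predictable effect of the drug. If significant symptoms are reported, dexamethasone may be taken on the investigators' advice, the patient is seen that day or the next working day, data are recorded, and "the subject asked to stop the mifepristone and withdrawn". Section 4 (Background) says that 1 mg of dexamethasone is enough to overcome 400 mg of mifepristone.

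Section 8.0 (Interruption or discontinuation of treatment) requires end-of-study evaluations for treatment failures, but only final safety evaluations for others who stop early. It lists ten possible reasons for stopping.

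**The concern.** The outcome is defined at 8 weeks, but the rule lets a value from another time stand in for it without saying which value. A phrase such as *at least one* does not choose between the last, the worst, the nearest or several values, so two analysts could follow the protocol and report different results.

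The substitution is also unlikely to be neutral. One route to withdrawal that the protocol itself describes runs through the drug's own action and may involve an agent said to reverse that action. A reading taken during symptoms, or after dexamethasone, does not represent eight weeks of mifepristone.

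The pilot has two purposes, stated in sections 5.3 and 11: to look for a trend and judge tolerability, and to supply an effect size for planning. A rule that can score a patient who could not tolerate treatment as an 8-week success blurs both.

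**Working it through.** The protocol gives no power calculation, SD, withdrawal rate or success threshold, so there is no figure of its own to reproduce. The check sets the rule against the schedule and then does the arithmetic for n = 6 (section 5.2).

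**1. What can be carried, by endpoint**

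| Endpoint | Scheduled after baseline | Earliest scheduled value that could stand as week 8 | Patient leaving before week 4 |
|---|---|---|---|
| Resting BP | each visit: weeks 1, 2, 3, 4, 6, 8 | week 1 | has a value if seen at week 1 or later |
| Ambulatory BP | weeks 4 and 8 | week 4 | no scheduled value |
| 2-hour glucose | weeks 4 and 8 | week 4 | no scheduled value |

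The resting BP row rests on the text of sections 5.2 and 5.8, because the marks in the visit table are not legible in the copy reviewed. A patient leaving at week 2 therefore enters the ITT set through resting BP, yet may have nothing to carry for the other two measures. The possible exception is a treatment failure whose end-of-study evaluations include ambulatory BP and an OGTT. The protocol does not say whether they do.

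**2. Effect on the success proportion**

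Let w patients withdraw and r of the 6 − w completers succeed.

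- Carried values all counted as success: (r + w)/6
- Withdrawals counted as non-success: r/6
- Completers only: r/(6 − w)

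The first two differ by w/6, that is 1/6 = 16.7 points per withdrawn patient.

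| Assumed case | Carried = success | Withdrawn = non-success | Completers only |
|---|---|---|---|
| w = 1, r = 3 | 4/6 = 66.7% (95% CI 22.3 to 95.7) | 3/6 = 50.0% (11.8 to 88.2) | 3/5 = 60.0% |
| w = 2, r = 2 | 4/6 = 66.7% | 2/6 = 33.3% | 2/4 = 50.0% |

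The intervals are Clopper-Pearson.

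**3. Effect on a mean change, if the rule is applied there too**

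Section 5.4 words the end points as differences, so the mean also matters. Assume that completers average −10 mmHg. This borrows, for illustration only, the systolic fall that section 4 reports after adrenalectomy. Let each carried value be v.

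- One withdrawal: (5 × (−10) + v)/6. With v = −30 this is −80/6 = −13.3; with v = +10 it is −40/6 = −6.7.
- Two withdrawals: (4 × (−10) + 2v)/6. With v = −30 this is −100/6 = −16.7; with v = +10 it is −20/6 = −3.3.

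The shift can go in either direction.

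**4. How often the rule would be used**

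The chance of at least one withdrawal among six is 1 − (1 − p)^6. At assumed per-patient rates of 5%, 10%, 20% and 30% this gives 26.5%, 46.9%, 73.8% and 88.2%.

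**The case against.** The strongest defence is that this is a six-patient, single-arm pilot with no formal testing. Each patient's course can be listed, withdrawals and adverse events are already recorded with reasons, and the rule does nothing unless someone leaves. That stands, and it limits the consequence. It does not make the rule workable, because the rule is the protocol's stated step on the way to its primary variable.

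A reader might infer several stronger things that the documents do not support.

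- *Efficacy would be inflated.* The direction is open. A reading at the height of blockade could flatter the drug, while one after dexamethasone could hide its effect. Hypotension is not among the symptoms that section 5.2 lists, so a harmfully low carried BP is conjecture.
- *Deficiency is the expected reason for leaving.* It is one route among ten listed reasons, and section 5.2 says the dose was chosen to avoid overt deficiency. Informative missingness is plausible, but its frequency is unknown.
- *No one leaving before week 4 could have an ambulatory BP or OGTT value.* End-of-study evaluations for treatment failures might supply one.
- *Week-1 values are a general problem.* They concern resting BP only. If the rule meant the last value, a week-1 reading would be used only for a patient leaving before week 2. The text does not say last, however.
- *The ITT and PP wording is itself an error.* Requiring one post-baseline value is a common modified-ITT definition, and an SAP commonly settles which set leads.

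**Conclusion.** The rule is badly fixed and should be changed. It is stated in the protocol, so it is not a detail left to an SAP. It names no visit and sets no minimum exposure, it does not fit the week-4 and week-8 schedule of two of the three primary measures, and it does not exclude readings affected by symptoms or by dexamethasone.

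The size is up to 16.7 percentage points of the success proportion per withdrawn patient. That figure needs only n = 6. The mmHg ranges and the withdrawal probabilities rest on assumed inputs and show scale, not expectation. With intervals as wide as those above, no conclusion from this pilot would be firm in any case. The practical harm is a misleading effect size passed to the next study and a blurred tolerability result. This is worth correcting before analysis but is not critical for a descriptive pilot.

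**What to change.** 1. Delete the carry-forward sentence from section 8.0 (Efficacy evaluation).
2. Report observed on-treatment values for all treated patients at their actual week, 4 and 8, with n at each. Do not present an earlier reading as week 8.
3. State that BP and glucose readings taken after dexamethasone are not used for efficacy.
4. List every withdrawal with its time, its reason and any dexamethasone use, and report it as a tolerability outcome beside efficacy.
5. For the 8-week success proportion, count withdrawn patients as non-successes and show the completers-only figure alongside.

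A repeated-measures model is not a good substitute. In six patients it would rest on a missing-at-random assumption that the deficiency-symptom route makes doubtful.

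The cost is wording only; no visit or measurement is added. The downsides are small: fewer than six observed week-8 values if a patient withdraws, and possibly a lower success proportion.

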**9: Involvement of service users**

This is not anticipated from this pilot study

**10: Methods for disseminating research results**

This is pilot study and thus will not provide a definitive answer. Nevertheless, research findings will be disseminated by presentation at National and International meetings in both Endocrine and Cardiovascular areas, and by scientific publication, as and when appropriate. Engagement with the media will be facilitated by [name]’s close working relationship with the UK Society for Endocrinology and US Endocrine Society, and their respective patient representation. [name] is a trustee of UK-based patient charities.

**11: Strategy for taking the work forward if the research project is productive**

If pharmacological glucocorticoid receptor antagonism of patients with SCS in this study improves blood pressure and or glucose tolerance, this would pave the way for larger study using mifepristone (MRC application) and ultimately a formal intervention study with adrenalectomy in such patients. The magnitude of any effect observed would be used to inform the size of study. This would be planned by collaboration with the larger endocrine community in the UK and abroad to assess the potential for generalising the findings. A multi-centre study involving major endocrine centres with the expertise of laparoscopic adrenalectomy would be proposed, with the response to glucocorticoid antagonism prior to adrenalectomy to be correlated to overall outcome, and to specifically answer the question whether this results in an accurate way of stratifying patients to proceeding to this irreversible procedure. Our study design will also allow identification of a marker that best correlates with effective glucocorticoid antagonism and outcome. In certain patients at high operative risk pharmacological glucocorticoid receptor antagonism may be appropriate for longer-term therapy, and the effectiveness of this approach would need a study in larger populations.

**12: Intellectual Property arrangements**

A positive outcome from this study would have significant clinical implications. The next step would be to plan a formal intervention study including glucocorticoid antagonism followed by adrenalectomy. Biofusion PLC, the University of Sheffield’s partner in commercialisation, has already carried out an initial patent search (Derwent Innovations Index & Patent Hunter) and believes that mifepristone treatment of sub-clinical Cushing’s to be potentially novel and patentable – thus any commercial exploitation will accrue commercial benefit for the partners in this project, and ultimately UK PLC. It should be noted that Biofusion PLC and Medipex NHS Innovations have an excellent relationship and record of working together taking innovations to market and it is envisaged that they will work together on this project. It should also be noted that there are other companies that are in the pre-clinical stage of developing glucocorticoid receptor antagonists to which the results of this trial will be relevant. Thus, we believe that the investigators of this study will be in a good position to exploit a positive outcome of this study.

